## Abstract

**Background:**

Food insecurity (FI) is associated with poorer physical and mental health outcomes, exacerbation of chronic diseases, and decreased access to healthcare. Children experiencing FI face additional risks, including lower psychosocial functioning and reduced academic achievement. Although national initiatives call for integrating nutrition support services into healthcare, clinical workflows for FI screening and referral remain inconsistently implemented and difficult to sustain. The goal of this study is to refine, adapt, and optimize a comprehensive FI screening and referral program, and identify effective implementation strategies for pediatric healthcare systems.

**Methods:**

We will use a RollOut Implementation and Optimization (ROIO) trial design to iteratively implement and refine the implementation strategies for our FI screening and referral program (I-FRESH: Implementing Food Referrals for Equity and Sustained Health) across 4 pediatric clinics. I-FRESH includes: (1) FI screening; (2) assessment of family needs and readiness to access services; (3) referral and navigation support to community nutrition programs; and (4) follow-up to assess fit, utilization, and ongoing needs. The Pragmatic, Robust Implementation and Sustainability Model (PRISM) will guide adaptation and evaluation of contextual determinants, while RE-AIM will guide assessment of outcomes (implementation feasibility and acceptability, fidelity, adoption, reach, effectiveness, and maintenance). We will identify several implementation strategies to increase the likelihood that I-FRESH can be successfully implemented and sustained in a pediatric healthcare system. We will enroll 240 participants and assess preliminary effectiveness on family‑level food security and pediatric nutrition‑related health outcomes (e.g. weight status, blood pressure, lipids, HbA1c, liver function tests). The information gathered in this trial will be utilized in the development of a fully powered Type 2 Hybrid Effectiveness-Implementation Trial that will test the effectiveness of the identified implementation strategies and impact of the FI program on clinical outcomes.

**Discussion:**

By integrating PRISM and RE-AIM within an iterative ROIO design, this study will generate a scalable, contextresponsive implementation model for addressing FI in pediatric healthcare settings. Findings will inform sustainable strategies that link families to highquality nutrition support programs and improve nutritionrelated health outcomes for lowincome children.

**Trial registration:**

NCT06661538.

Contributions to the literature• The Roll-Out Implementation and Optimization trial design allows us to quickly and continuously learn and adapt workflows across sites and identify effective strategies to implement a food insecurity screening and referral process that is not confounded by time and system-level changes.• This design allows us to examine the impact of strategies within clinics over time and between clinics at each time point.• This study uses community engagement methods to gather healthcare providers and staff, community-based nutrition support programs, and implementation science researchers to address the complex issue of connecting patients with health-related social-needs to appropriate community programs.

## Background

Food insecurity (FI), defined as limited or uncertain access to adequate food [1], is associated with poorer physical and mental health outcomes in adults [2–4], greater financial hardship, and decreased access to care [5]. Children experiencing FI also have poorer health outcomes [6], lower psychosocial functioning [7–9], and lower academic achievement [10]. FI exacerbates chronic health conditions such as liver disease and cardiovascular disease (CVD) [2, 11]. Furthermore, individuals with obesity and poor dietary intake have greater likelihood of developing type 2 diabetes mellitus (T2D), CVD, and cancer [12]. Given the wide reaching impact of good nutrition, Healthy People 2030 identified reducing FI as a top priority to improve health [13].

Access to healthy foods, such as fresh fruits and vegetables, whole grains, nuts, and lean proteins (e.g., Mediterranean diet, DASH diet) are associated with reduced incidence of CVD, T2D, cancer, neurodegenerative disease, and overall mortality [14–16]. Food assistance programs, such as Supplemental Nutrition Assistance Program (SNAP), may moderate these health risks by increasing access to food for those with limited incomes [17]. Other programs, including WIC, school meal programs, and community-based food assistance programs such as food banks also improve access to food, dietary quality, and school-related and developmental outcomes for children [18–21].

In recent years, healthcare systems have increasingly been called upon to implement screening for a wide range of adverse social determinants of health (SDOH). In 2022, The White House Conference on Hunger, Nutrition, and Health underscored the critical role of integrating nutrition support programs and education into the healthcare setting to address food security [22]. To achieve this integration, healthcare systems are encouraged to follow a two-step process: 1) identify the unmet social need and 2) link patients to appropriate services [23]. Despite the simplicity and clarity of this charge, this workflow can be challenging to implement with little consensus on the most effective and sustainable ways to integrate these procedures into current clinical workflows [24–26].

Several barriers hinder successful screening and referral processes in the clinical setting, including technical challenges, difficulties in maintaining fidelity within complex workflows, and constraints on personnel. Additionally, connecting families with community-based programs can be challenging, particularly when there is limited knowledge among healthcare providers about which programs are reliable and provide high-quality services [27]. Furthermore, simply providing program information to families may not be effective. Without comprehensive service navigation (e.g., by a social worker or care navigator who actively assists families in accessing programs) or follow-up communication from community organizations to confirm program utilization, it remains unclear whether referrals alone lead to meaningful health improvements [24, 27].

The purpose of the study is to refine, adapt, and optimize a screening and referral process to address FI in the pediatric healthcare setting. The proposed **I-FRESH (Implementing Food Referrals for Equity and Sustained Health)** program involves screening for FI and referring families to appropriate nutrition support programs in the community. Given that the I-FRESH workflow has not been fully developed or tested in its entirety, we will refine, adapt, and optimize the full workflow and identify implementation strategies using an iterative process defined by the **Roll-Out Implementation and Optimization (ROIO)** study design (Fig. 1). This study design allows us to identify implementation strategies that work in one clinic, and then refine, adapt, and optimize these implementation strategies in the next iteration of the program in the next clinic. We will optimize this workflow over 4 different clinics within the healthcare system and examine implementation and clinical effectiveness outcomes during each phase of the roll-out. The planned components of I-FRESH include: 1) screening and identification of families experiencing FI in the health care setting; 2) social worker or care navigator-led discussions with families to determine need and readiness to receive support; 3) referrals and assistance from allied health professionals or care navigators to engage with community programs and resources; and 4) follow-up assessments to determine program fit, track utilization, and determine need for additional referrals. The implementation strategies will: 1) use tools available in the electronic health record (EHR) to increase efficiency and scalability, and 2) address communication and care navigation failures (Fig. 2).

**Fig. 1 Fig1:**
[figure not shown]
Roll-Out Implementation and Optimization design for the I-FRESH trial. Four clinics will participate in this roll-out implementation and optimization trial. Refinement and adaptation of strategies will occur before implementing I-FRESH in each clinic, and will be based on learnings from the prior clinic’s implementation effort. Implementation and clinical effectiveness outcomes will be measured across each clinic. The Pragmatic, Robust Implementation and Sustainability Model (PRISM) will be used to guide the refinement, optimization, implementation, and evaluation process, and the Reach, Effectiveness, Adoption, Implementation, and Maintenance (RE-AIM) outcomes framework will be used to evaluate core implementation outcomes, including feasibility, acceptability, fidelity, adoption, reach, and effectiveness

**Fig. 2 Fig2:**
[figure not shown]
I-FRESH intervention components and implementation strategies. The planned intervention components are listed across the top in green. Below each intervention component are the planned implementation strategies. Proposed implementation strategies that may need further refinement are indicated with a “*”. All components and strategies may be modified during the refinement and optimization process. The Pragmatic, Robust Implementation and Sustainability Model (PRISM) and Reach, Effectiveness, Adoption, Implementation, and Maintenance (RE-AIM) framework will be used to guide the implementation process and evaluation

## PRISM/RE-AIM implementation framework

We will use the **Pragmatic, Robust Implementation and Sustainability Model** (**PRISM**) to guide refinement, optimization, implementation, and evaluation [28, 29]. PRISM allows for systematic, multi-level consideration of factors and contexts that are relevant for implementation success, such as characteristics of program recipients, intervention characteristics, implementation and sustainability infrastructure within the healthcare system and nutrition support programs, and the external federal and state environment that create guidelines and regulations. Refinements and adaptations can then be made to increase the likelihood of program sustainability. By considering the inner and outer contexts that influence how and in what form I-FRESH will be implemented [30, 31], we will outline an effective implementation process model for our healthcare system that addresses FI and provides added health benefits for low-income patients with nutrition-related conditions.

The **Reach, Effectiveness, Adoption, Implementation, and Maintenance** (**RE-AIM**) outcomes framework [32, 33] will be used to evaluate core implementation outcomes, including feasibility, acceptability, fidelity, adoption, reach, and effectiveness. More specifically, we will evaluate the extent to which the intervention reaches eligible patients, is adopted or accepted by different clinical staff, can be delivered with fidelity after adaptations, and can be integrated and sustained in routine pediatric healthcare. Clinical effectiveness outcomes include impact on family-level FI and child health-related outcomes. Together, PRISM and RE-AIM enable a comprehensive, real-world assessment of implementation determinants, processes, and clinical effectiveness.

The specific aims of this study are:To engage our Community, Clinical, Administrative, and Research Advisory Board (CARAB) to *refine and optimize* the program before and after each roll-out in 4 clinics and identify factors in the inner and outer context that serve as barriers and facilitators to engaging in the program.To assess *implementation outcomes* of our comprehensive nutrition support program and determine:*Feasibility and acceptability* of I-FRESH by families, healthcare providers, ancillary support staff, administrators, community nutrition support programs, and community members, and*Fidelity, adoption, and reach* of the program by assessing which components were carried out by ancillary staff/care navigator, staff/setting characteristics, and percentage of families who participated.To examine *preliminary effectiveness outcomes* on family-level FI and pediatric nutrition-related health outcomes, such as, weight status, blood pressure, lipids, HbA1c, and liver function tests. We will also assess changes in medication dose or type (e.g., stopping insulin and only requiring metformin) and engagement in recommended services (e.g., decrease in no-show rates).

We hypothesize feedback and adaptations will develop an implementation bundle that is feasible and acceptable to families, staff, healthcare providers, hospital administrators, and community nutrition support programs. Our goal is to have a robust, feasible, and scalable program that can be tested in a fully powered Type 2 Hybrid Effectiveness-Implementation Trial.

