### Study objectives

#### Specific Aim 1: Refinements and adaptations: implementation Mapping

The goal for Aim 1 is to identify which components of the I-FRESH intervention and implementation strategies are effective and which intervention components and implementation strategies need to be modified to increase the impact of I-FRESH for different populations in different clinic settings. This information will help to identify which program components and implementation strategies are key to program success and should be prioritized when implemented across diverse settings and external contexts. We will use the Implementation Mapping [35] approach to develop expected implementation outcomes for the RE-AIM domains of adoption, implementation, fidelity, and maintenance.

Prior to the first roll-out, we will engage CARAB and other key stakeholders to participate in a brainwriting premortem [41] discussion to refine the program structure and identify potential barriers and facilitators to implementing the full workflow. During this this co-production process [42], participants with expertise in implementation science, clinical informatics, behavior change, and historical evidence behind implementing such a program will be able to discuss with those who have detailed knowledge of the logistics of implementing such a program in the hospital and its EHR, and those who have expertise around the community/family perspectives and context. During this process, modifications to implementation strategies, program content, format of delivery, and timing of program components will be made as needed. Barriers to optimizing fidelity and reach (be it from the internal or external context/environment) will be identified, documented, and addressed when possible. Program materials and protocols will be adapted to foster multiple levels of communication and information sharing between families, the health system, and community programs. Finally, existing materials, referrals, and resources will be modified to make them more user friendly for the English and Spanish-speaking populations. Members of the CARAB will provide input on all these modifications and review program materials before they are implemented.

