#### Specific Aim 2: Assess implementation outcomes

With each iteration of the roll-out, we will gather implementation outcomes from each level of the program: individual/family, hospital, and community partner level. Using the RE-AIM outcomes framework [32, 33], our primary implementation outcomes are feasibility and acceptability of I-FRESH by families, healthcare providers, ancillary support staff, administrators, community nutrition support programs, and community members. We will also assess fidelity, adoption, and reach of the program by assessing which components were carried out by ancillary health care staff/care navigator, staff/setting characteristics, and percentage of families who participated. Reach and maintenance of the program will be tracked through the EHR registry. (Further details on assessments are presented below in Measures.)

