#### Quantitative data

Primary analyses for Aim 2 will assess fidelity and reach outcomes (Aim 2b) assessed within the EHR (e.g., screening, referrals, and follow-up assessments) and surveys (e.g., Acceptability, Feasibility, and Appropriateness) across the study period using Generalized Linear Mixed-effects Models (GLMM) and time-varying indices for clinics randomized to cross-over in each wave, time (secular trend), and clinic characteristics as planned covariates. Serial cross-sectional summaries for each clinic within monthly blocks will allow estimation of changes in clinic outcomes after crossing over into interventions. Primary analyses for Aim 3 will describe I-FRESH participants’ (*n* = 240) changes in health outcomes including: a) metabolic labs, BP, BMI, b) healthcare utilization; c) community program utilization; d) Quality of Life; e) Food Frequency Questionnaire and f) Knowledge, Skills, Attitudes, and Self-Efficacy. GLMM growth models for individual trajectories of continuous and limited categorical outcomes will include a focus on significance of changes from baseline to post-treatment assessments after graphically examining an appropriate functional form (e.g., linear or categorical) for modeling each outcome. All models will include participants’ characteristics (gender, ethnicity, parental education) and allocation clinic as planned covariates when estimating changes in primary health and engagement outcomes. We will explore the role of SDOH and implementation strategy effectiveness as potential influences in describing changes in parent and child health outcomes. Benjamini-Hochberg [78] procedures will be used to adjust *p*-values for inference decisions within common domains.

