##### Power considerations

We conducted power/sample size for this ROIO design trial to address primary aims, using developed formulas [81] drawn from stepped wedge designs that account for unequal cluster size and package *swCRTdesign* [82]. The design includes 4 identified clinics (clusters), at least one 3-month period in standard care and 4 additional periods where assigned clinics can transition to I-FRESH at 4-month intervals. We estimated the needed sample to test a 10% difference in proportions of engagement in services (i.e., Aim 2b healthcare and community program utilization), and a standardized mean increase of at least d ≥ 0.20 when reported at 6- and 12-month health outcomes. With alpha = 0.05, 4 clusters (1 clinic per cluster = 4 clinics with *n* = 300 - 500 potential patients in each clinic) and five periods of transitions (baseline and 4 clinics), we will maintain power > 0.83 to detect clinic differences (I-FRESH vs standard care) of >8% in rates of screening, referral and follow-up engagement in services and changes in acceptability ratings of d > 0.20 after implementing I-FRESH given a between clinic standard deviation of 0.05 in random treatment effects. Using an empirical approach, we simulated 1000 data sets with expected mean changes (d ≥ 0.20) and serial correlations similar to pilot samples. We used the percentage of growth models with *p* < 0.05 for slope parameters to estimate power given proposed sample of 60 per clinic and allowance for 20% missing data. With median slope of 0.02 (increase per month; estimate sd = 0.01) we observed significant effects in >81% of models suggesting sufficient power to detect desired effects in Aim 3 with the proposed sample.

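### Feasibility and acceptability are hypothesised as a level reached, but the stated analysis and power target for these ratings concern change after cross-over

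*Protocol article*

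**What the plan says.** All references are to the protocol article.

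- **Hypothesis** (specific aims, under PRISM/RE-AIM implementation framework): "We hypothesize feedback and adaptations will develop an implementation bundle that is feasible and acceptable to families, staff, healthcare providers, hospital administrators". The list goes on to community nutrition programmes. No comparator is named. The stated goal is a programme fit to be tested in a fully powered Type 2 hybrid trial.
- **Primary outcomes** (Specific Aim 2): "our primary implementation outcomes are feasibility and acceptability of I-FRESH by families, healthcare providers, ancillary support staff, administrators", followed by community programmes and community members.
- **Analysis** (Quantitative data): "Primary analyses for Aim 2 will assess fidelity and reach outcomes (Aim 2b) assessed within the EHR". The same sentence adds the acceptability, feasibility and appropriateness surveys to the mixed model, with time-varying cross-over terms. Then: "Serial cross-sectional summaries for each clinic within monthly blocks will allow estimation of changes in clinic outcomes after crossing over into interventions".
- **Power** (Power considerations): power above 0.83 at alpha 0.05 for "changes in acceptability ratings of d > 0.20 after implementing I-FRESH".
- **Timing** (Program acceptability, feasibility, and process evaluation; Table 1): parents, 60 per clinic, are surveyed after referral and programme use, at 6 and 12 months. Staff surveys are post-roll-out, every 6 months. Table 1 gives 6 and 12 months for these measures.
- **Targets** (Specific Aim 1): Implementation Mapping will "develop expected implementation outcomes for the RE-AIM domains of adoption, implementation, fidelity, and maintenance".

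**The concern.** A hypothesis that a bundle is feasible and acceptable is answered by how high the ratings are. A cross-over model asks whether they moved. The two can disagree: ratings that rise from poor to slightly less poor can be significant, while ratings that are high throughout show no change. If the change result is what gets reported for the primary implementation outcomes, readers and the planners of the next trial will have a p-value that does not bear on the hypothesis. The power statement would meanwhile suggest that the hypothesis had been provided for.

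The schedule adds a second problem. A change from standard care needs ratings made under standard care, and the article describes none for these instruments.

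**Working it through.** **1. The passages side by side**

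| Element | Section | Quantity |
|---|---|---|
| Hypothesis | Specific aims | Level: feasible and acceptable |
| Primary implementation outcomes | Specific Aim 2 | Feasibility and acceptability |
| Analysis | Quantitative data | Change after cross-over |
| Power target | Power considerations | Change, d > 0.20 |
| Collection | Process evaluation; Table 1 | After roll-out only |

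The first two rows and the last fit together. The third and fourth do not fit them.

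**2. The plan's own power figure**

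Stated inputs: 4 clinics, 5 periods, alpha 0.05, treatment-effect SD 0.05, 300 to 500 potential patients per clinic. The number of raters per clinic-period and the between-clinic intercept SD are not given, so the figure above 0.83 cannot be reproduced uniquely. I used a cross-sectional stepped-wedge mixed model with one clinic crossing per step, unit residual SD, a two-sided test, and intercept SD assumed between 0.05 and 0.22:

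| Raters per clinic-period | Power for d = 0.20 |
|---|---|
| 300 | 0.96 to 0.98 |
| 60 | 0.47 to 0.57 |
| 12 (60 per clinic over 5 periods) | 0.15 to 0.18 |

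The point does not rest on this table. It shows only that the stated power for acceptability depends on a rater count that the article does not give.

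**3. What the change test can and cannot show**

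Take the stated power at face value. Implied SE of d = 0.20 / (z at 0.83 + z at 0.975) = 0.20 / (0.954 + 1.960) = 0.0686. The chance of two-sided p < 0.05 is then 5% at d = 0, 31% at d = 0.10 and 83% at d = 0.20. The starting level does not enter. With an assumed rating SD of 0.8 points, d = 0.20 is 0.16 points. A move from 2.0 to 2.16 and a move from 4.2 to 4.36 have the same chance of significance.

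**4. What a level estimate would deliver**

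Parents: 60 × 4 = 240; less the planned 20% loss, 240 × 0.8 = 192. Half-width = 1.96 × √(p(1 − p)/n), clustering ignored:

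- p = 0.70: 1.96 × √(0.21/192) = 6.5 points. Exact interval at 134 of 192: 62.8 to 76.2%.
- p = 0.75: 1.96 × √(0.1875/192) = 6.1 points. Exact interval at 144 of 192: 68.3 to 81.0%.
- One clinic, 60 × 0.8 = 48 parents: 13.0 points at 70%, 12.3 at 75%.

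Staff and stakeholders: up to 100 in all (Participants). Assuming an even split over the five non-family groups in Specific Aim 2, that is about 20 each: 20.1 points at 70%, 19.0 at 75%.

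**5. Would a lower-bound pass rule work in every group?**

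No. At an illustrative 70% mark and an exact 95% lower bound, 18 of 20 fails (68.3%) and 19 of 20 passes (75.1%). A group with 85% true agreement passes about 18% of the time. At about 5 raters per group per clinic (20 / 4), unanimous agreement gives a lower bound of 48%.

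**The case against.** **A benchmark may exist elsewhere.** This is a condensed article, and a cut-off on a rating scale is commonly left to the full protocol or SAP. That stands. A reader might infer that no pass mark exists and that the hypothesis therefore cannot be decided or cannot fail. The article supports only that it states none. A benchmark held elsewhere would still not make a change test answer a level hypothesis.

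**Implementation Mapping may already cover these outcomes.** Specific Aim 1 lists implementation separately from fidelity, and the abstract pairs implementation with feasibility and acceptability. Table 1 instead joins implementation with fidelity. The text is ambiguous, so a reader who takes Specific Aim 1 to exclude these two outcomes goes further than it allows.

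**The article never equates significance with feasibility.** That is correct. Levels can still be described from the surveys, the monthly summaries, the interviews and the joint display. The fault lies in which quantity receives the stated inference and power.

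**Change matters in an optimisation design.** It does: whether ratings improve as strategies are refined is a fair question. That is a reason to keep the trend as a secondary estimate. It does not make the trend an answer to the hypothesis.

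**The effectiveness outcomes are exploratory.** Specific Aim 3 says so of the clinical outcomes. Feasibility and acceptability are called primary, and acceptability is given a power target.

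**Conclusion.** The mismatch is real and rests on what the article states. The hypothesis and primary implementation outcomes concern a level. The quantitative analysis and power target for the same ratings concern change, and the described data collection is post-roll-out only. A lesser inconsistency accompanies it: the primary-analysis sentence leads with fidelity and reach, while Specific Aim 2 gives primary status to feasibility and acceptability.

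The finding does not extend to a claim that the primary question is undecidable, nor does it support a formal pass test in each rater group. The size of any error in the final conclusion cannot be given, because it depends on ratings not yet collected and on a benchmark the article does not state. What can be sized is the replacement: useful precision for pooled parents and poor precision for small groups. Those figures assume 192 independent parents and an even split of 100 stakeholders; clustering by clinic would widen them.

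**What to change.** 1. **Quantitative data.** Make the post-roll-out level of acceptability, feasibility and appropriateness (mean or percentage agreeing) the primary estimate for these outcomes. Give it with a 95% confidence interval, overall and by rater group, allowing for clinic. Keep change or trend across roll-outs as secondary.
2. **Power considerations.** Replace the d > 0.20 acceptability statement with expected precision: about 6 to 7 points for 192 parents at 70 to 75% agreement before clustering. State that staff and community groups will be much less precise and will be reported descriptively.
3. **Benchmark, if one is used.** The sponsor and the advisory board should set it before the first roll-out; the Implementation Mapping step is a natural place. Apply it to the point estimate or to the pooled parent sample, not as a lower-bound test in every small group or clinic.

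The cost is wording in two sections and, if a benchmark is wanted, one decision before roll-out. No new data, visits or participants are needed.
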